#### Phase 2. Study of PROSPECTIVE cohorts, assigned by randomised blocks

The study will be initiated with two cohorts:

1.
***Exposed cohort*****:** comprising patients who will be attended by SAIATU, without prejudice to the care received from the public health system.

2.
***Control cohort*****:** comprising patients who will be cared for exclusively through the public health system.

The evolution of the disease over the course of the study will determine the different healthcare mechanisms (Primary Care, Specialised Care (SC), Home Hospitalisation (HH)) that will intervene in the care of each patient, so that, at the end of the study, the two initial cohorts will be divided into 4 subgroups:

1)
*Exposed cohort*

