### Specific objectives

- Describe the average profile of healthcare resource consumption of a retrospective cohort (patients who died from malignant neoplasm) in the last 30 days of life by diagnosis and age group.

- Quantify and compare the costs of the use of healthcare resources in the cohorts of patients with and without SAIATU intervention.

- Compare quality of life in the cohorts of patients with and without SAIATU intervention.

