#### Phase 1: RETROSPECTIVE study to register a control cohort of patients who died from malignant neoplasm

The objective of this study is to determine the baseline risk of the principal variable, *consumption of resources* in the population of patients who die from malignant neoplasm.

Thus, the study characterises, by primary diagnosis (criteria and rules established by the International Statistical Classification of Diseases 10 [ICD-10] [26]) and age, the behaviour of different malignant neoplasms, with regard to resource consumption: number of visits to or consultations with Primary Care, number of external consultations, number of visits to hospital emergency departments, number of hospital admissions, average length of stay, and days in home hospitalisation.

Time of study: time series of 4 years, to be determined based on Osakidetza records and the mortality register.

Based on the results of this study and on the hypothesis of the decrease in, and improved efficiency of, resource consumption through the intervention of support programs, formulated as a result of the retrospective observational study carried out, the sample size of cohorts and subgroups will be defined for Phase 2: PROSPECTIVE cohort study.

For this analysis, the error will be established at α = 5% with a statistical significance of 80% (error β = 20%). The sample size of each subgroup *n* will be the maximum of the sample sizes obtained for the comparison of means or proportions of the main variables in each subgroup.

For the comparison of two means:

(1)$$n\;=\;\left(2\left[\left(\mathrm{Z\alpha}/2+\mathrm{Z\beta}\right)\right]\wedge 2*\text{S}\wedge 2\right)/\text{d}\wedge 2$$

where:

(2)$$\begin{array}{l} \mathrm{Z\alpha}/2\;=\;1.960\\ \mathrm{Z\beta}\;=\;0.842 \end{array}$$

S^2^ = variance in the quantitative variable of the control group

d = Minimum value of the difference to be detected (quantitative values)

For the comparison of two proportions:

(3)$$n\;=\;2p*q\wedge 2\left(\mathrm{Z\alpha}/2+\mathrm{Z\beta}\right)\wedge 2/\left(\mathrm{pA}-\mathrm{pB}\right)\wedge 2$$

where:

(4)$$\begin{array}{l} \mathrm{Z\alpha}/2=1.960\\ \mathrm{Z\beta}=0.842 \end{array}$$

p = Mean of the two proportions pA y pB

The parameters will be analysed with the statistical software SPSS 15.0 for Windows.

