### Population for Study

This study will comprise oncology patients from the health districts of Guipúzcoa, attended by the Basque Health Service.

Assuming that 2,500 people per million population die each year from malignant neoplasm, and taking into account that the population of Guipúzcoa is 709,607 inhabitants, it is estimated that the eligible population for this study is 1,774 deaths from malignant neoplasm per year. For a period of 10 months of prospective study, this corresponds to a population of 1,478 deaths from malignant neoplasm in these provinces.

Although the final number of patients for inclusion will be calculated during the design of the prospective study itself, after the results of Phase 1, it is estimated that the resulting sample size could allow some 150 patients to be studied. This sample, which would correspond to 10% of the total population of deaths from cancer in this period, would strengthen the study’s feasibility with respect to its representativeness of the total population in both provinces.

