### Analysis of variables

The parameters will be analysed using the statistical software SPSS 15.0 for Windows.

A descriptive study will be conducted on the *consumption of healthcare resources* by subgroup in the last 30 days of life. The descriptive study will include measures of central tendency, confidence intervals at 95% for the population mean, and contingency tables (frequencies) for each of the recorded variables.

Each subgroup will be analysed by age, sex, and main diagnosis.

For the comparison of proportions, Pearson’s Χ^2^ test, or, when appropriate, Fisher’s exact test will be used to calculate relative risk (RR), absolute risk reduction (ARR) and the number needed to treat (NNT) with 95% confidence interval.

The Student T-test will be applied to calculate the equality of means for independent samples in the case of continuous variables, upon confirmation of the conditions of normality and homoscedasticity.

The quantification of costs incurred by the SAIATU program will be calculated on the basis of the activities performed by the program’s professionals, measured in hours of care. Based on the actual time spent on patients, the total cost will be distributed between each of the activities.

Calculations of unit costs per activity, taking into account the number of times each activity is performed for the period under analysis, will finally be performed.

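### Sample size is set, and the main variable reported, by subgroups formed after allocation by use of home hospitalisation, and the tests name no contrast

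*Protocol article*

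**What the plan says.** The Phase 2 section of the protocol article assigns patients to an exposed and a control cohort by randomised blocks. It adds that the course of the disease will decide which services take part in each patient's care, so that "at the end of the study, the two initial cohorts will be divided into 4 subgroups". The list that follows shows that the split is HH or no HH within each cohort.

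The Phase 1 section says that the sizes of both cohorts and subgroups will be derived for Phase 2. The only rule it gives is per subgroup: n "will be the maximum of the sample sizes obtained for the comparison of means or proportions of the main variables in each subgroup". The error rates are two-sided α = 5% and β = 20%; the 80% is labelled a significance level but is the power. The smallest difference to detect and the variance are defined without values.

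The section on analysis of variables describes resource consumption "by subgroup in the last 30 days of life" and then breaks each subgroup down by age, sex and diagnosis. The chi-squared, Fisher and t tests follow in separate paragraphs that do not say which groups are compared.

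The specific objectives ask about the two cohorts: "Quantify and compare the costs of the use of healthcare resources in the cohorts of patients with and without SAIATU intervention". The general objective, the hypothesis and the discussion are framed the same way. On numbers, "it is estimated that the resulting sample size could allow some 150 patients to be studied", with the final figure left until Phase 1 is complete.

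**The concern.** Randomisation makes the two cohorts comparable. It does not make HH users in one cohort comparable with HH users in the other, because HH use is decided later by the course of the disease and by the care given. The programme description presents SAIATU as support that enables clinical palliative teams to work in the home, in close co-ordination with home hospitalisation. An effect on HH use is therefore plausible, although the article does not claim one. HH visits and calls are also listed under the main variable, so the split conditions on a component of the outcome.

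Two things are at stake. First, if the unnamed tests were run within HH strata, a difference due to selection could be taken for a saving due to SAIATU, which is the study's central claim. Second, a sample-size rule tied to groups whose membership is unknown at enrolment cannot be met by recruiting to a target, since the disease course and clinical decisions determine how many patients fall in each group.

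**Working it through.** **Inputs from the protocol article.** Z for α/2 = 1.960 and Z for β = 0.842; formula (1), n = 2(1.960 + 0.842)²S²/d²; provisional total about 150; 2,500 cancer deaths per million and a population of 709,607.

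**Inputs assumed, because the article gives none.** 1:1 allocation (75 per cohort); HH share from 10% to 50%; differences in SD units; the correlations in the simulations below.

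**The plan's own figures.** 2,500 × 0.709607 = 1,774 deaths a year; × 10/12 = 1,478; 150/1,478 = 10.1%. These reproduce. The 150 cannot be obtained from formula (1), because d and S have no values. It is a feasibility figure, about 10% of expected deaths.

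**Detectable difference.** From formula (1), d/S = 2.802 × √(2/n):
- n = 75 (whole cohorts): 0.458
- n = 37.5 (HH users, 50% share): 0.647
- n = 22.5 (HH users, 30% share): 0.835

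**Power for 0.458 SD.** Power = Φ(0.458 × √(n/2) − 1.960). For n = 75 this is 80%, whatever the HH share. Within strata, with the same share in both cohorts:

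| HH share | HH users per cohort | Power, HH users | Power, non-users | Total N for at least 75 in every cell |
|---|---|---|---|---|
| 50% | 37.5 | 51% | 51% | 300 |
| 40% | 30 | 43% | 58% | 375 |
| 30% | 22.5 | 34% | 65% | 500 |
| 20% | 15 | 24% | 71% | 750 |
| 10% | 7.5 | 14% | 76% | 1,500 |

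The last column is 150 divided by the smaller of the HH and non-HH shares. If the shares differ by cohort (50% v 30%), power is 40% in HH users and 57% in non-users.

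**Bias from conditioning on HH.** A simulation of 2,000,000 patients gave SAIATU no effect on the outcome. Severity had correlation 0.7 with the propensity to use HH, and 0.3 or 0.5 with the outcome. Type I error is for 75 per cohort, two-sided 5%.

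| HH use, SAIATU v control | Correlation with outcome | Difference in HH users / non-users (SD) | Type I error, HH users / non-users |
|---|---|---|---|
| 30% v 30% | 0.3 and 0.5 | about 0 / about 0 | 5% / 5% |
| 50% v 30% | 0.3 | −0.08 / −0.06 | 6% / 6% |
| 50% v 30% | 0.5 | −0.12 / −0.11 | 8% / 8% |
| 60% v 30% | 0.3 | −0.11 / −0.10 | 7% / 7% |
| 60% v 30% | 0.5 | −0.18 / −0.17 | 11% / 12% |

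The comparison of whole cohorts was about 0 throughout. With SAIATU lowering HH use (30% v 50%) the sign reverses.

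A second model, in hospital days (SD 7.2), gave false reductions of 0.6 to 0.7 days at 50% v 36%, about 0.1 SD, and 1.26 days at 64% v 36%, or 1.26/7.2 = 0.175 SD.

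**Formula (3).** As printed it contains p × q². For 0.6 v 0.4 (p = q = 0.5) it gives 2 × 0.5 × 0.25 × 7.851/0.04 = 49 per group. With p × q, the usual form, it gives 98. This may be a typesetting slip, but it halves n here and should be checked before use.

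**The case against.** The strongest reply is that the article does not commit to testing within HH strata. The sentence on subgroups in the analysis section is explicitly descriptive (central tendency, confidence intervals, frequency tables), and the two-cohort comparison is a stated objective. This stands. A reader might infer that the whole analysis is built on the four subgroups, or that randomisation is broken. The documents support neither: a later split does not undo allocation, and only contrasts within HH strata lose its protection.

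A reader might also infer that 80% power cannot be planned at all. That goes too far. Phase 1 is to size cohorts as well as subgroups, and cohort power does not depend on the HH share. Phase 1 also records days in home hospitalisation, which could inform an expected share, so subgroup power can be planned under an assumption, though not assured. The 150 is provisional, and the article states no effect size against which 51% or 34% could be called a shortfall.

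The bias is conditional too. It would be wrong to say that stratifying on HH yields a false effect when SAIATU changes nothing: with equal HH use it was about zero in these models.

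Subgroup in Phase 1 might be read as diagnosis or age strata. That fits less well, because the text speaks of cohorts and subgroups for Phase 2, and the only ones defined there are the four.

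What the reply does not remove is that the one sizing rule given is per subgroup and that the tests name no contrast. These are features of the stated plan, not details left to a fuller document.

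**Conclusion.** The point holds in limited form. The stated sizing rule and the reporting of the main variable rest on subgroups defined by a post-allocation event that is part of the outcome, while the objectives ask about the two randomised cohorts. The analysis section does not connect its tests to that question.

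Within-stratum comparisons would be biased if SAIATU changes HH use, by about 0.1 to 0.2 SD with type I error of roughly 6% to 12% in the scenarios modelled. For 150 patients, the cohort comparison has 80% power at 0.46 SD; the same difference among HH users has about 51% power at a 50% share and 34% at 30%.

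The 1:1 ratio, HH shares, SD scale and correlations are all assumptions. That membership is fixed after allocation, and that subgroup sizes are unknown at enrolment, come directly from the article.

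**What to change.** In the Phase 1 sample-size text and the analysis section:

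- Name as primary the comparison of all patients assigned to SAIATU with all assigned to control, analysed as assigned whatever care they later receive, and state that the tests apply to this contrast.
- Apply formulas (1) and (3) per cohort, after checking the squared q in formula (3), and state the detectable difference. For 75 v 75 it is 0.46 SD.
- Report HH use by cohort as an outcome.
- Label the four-subgroup tables descriptive, with no between-arm tests.

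The cost is wording. No added data or patients are needed to make this change, and the final N has not yet been set. What is given up is any confirmatory claim about SAIATU within HH users or non-users.

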1.1. Patients attended by Primary Care + SC + SAIATU

2.2. Patients attended by Primary Care + SC + HH + SAIATU

2)
*Control cohort*

a. Patients attended by Primary Care + SC

b. Patients attended by Primary Care + SC + HH (Figure 1)

**Figure 1 F1:**
[figure not shown]
**Flow chart.** Study of prospective cohorts, assigned by randomised blocks.

### Population for Study

This study will comprise oncology patients from the health districts of Guipúzcoa, attended by the Basque Health Service.

Assuming that 2,500 people per million population die each year from malignant neoplasm, and taking into account that the population of Guipúzcoa is 709,607 inhabitants, it is estimated that the eligible population for this study is 1,774 deaths from malignant neoplasm per year. For a period of 10 months of prospective study, this corresponds to a population of 1,478 deaths from malignant neoplasm in these provinces.

Although the final number of patients for inclusion will be calculated during the design of the prospective study itself, after the results of Phase 1, it is estimated that the resulting sample size could allow some 150 patients to be studied. This sample, which would correspond to 10% of the total population of deaths from cancer in this period, would strengthen the study’s feasibility with respect to its representativeness of the total population in both provinces.

### Criteria for inclusion and exclusion from the study sample population

Criteria for inclusion:

- Documented presence of incurable, progressive and advanced oncological disease, capable of systematic treatment in the home.

- Little or no possibility of response to oncological treatment with a curative intent.

- Limited life prognosis.

- Presence of a principal carer.

Criteria for exclusion:

- Death or disability of the family carer.

- Withdrawal from the Basque public health system

- Absence of compliance with informed consent.

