**Method/design:**

Comparative prospective cohort study, with randomised selection of patients, which will systematically measure patient characteristics and their consumption of resources in the last 30 days of life, with and without the intervention of a social support team trained to provide in-home end-of-life care.

For a sample of approximately 150 patients, data regarding the consumption of public healthcare resources, SAIATU activity, home hospitalisation teams, and palliative care will be recorded. Such data will also include information dealing with the socio-demographic and clinical characteristics of the patients and attending carers, as well as particular characteristics of patient outcomes (Karnofsky Index), and of the outcomes of palliative care received (Palliative Outcome Scale).

Ethical approval for the study was given by the Clinical Research Ethics Committee of Euskadi (CREC-C) on 10 Dec 2012.

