### Variables and sources of information

#### Main variable: Consumption of resources

##### Primary and specialised care

Records of patient activity will be obtained from Osakidetza’s information systems.

The variables for analysis are the following:

- Number of nursing home visits.

- Number of visits to nursing home health clinics.

- Number of home visits by the family doctor.

- Number of visits to the family doctor’s clinic.

- Number of specialist outpatient consultations.

- Number of visits to hospital emergency departments.

- Number of hospital admissions.

- Number of days admitted to hospital.

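### Two exclusion criteria carry no time of application and read as events after assignment; applied that way, they may bias the randomised comparison

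*Protocol article*

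**What the plan says.** The relevant section of the Protocol article is headed "Criteria for inclusion and exclusion from the study sample population". One inclusion criterion is "Presence of a principal carer". The exclusion list has three items. Two concern this point: "Death or disability of the family carer" and "Withdrawal from the Basque public health system". The third concerns consent. No item has a time of application, and the section does not say what happens to a patient who meets one later.

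The Population for Study section already limits the study to oncology patients under the care of the Basque Health Service.

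Phase 2 is titled "Study of PROSPECTIVE cohorts, assigned by randomised blocks". The abstract gives the outcome as "consumption of resources in the last 30 days of life, with and without the intervention of a social support team". Among its components is "Number of days admitted to hospital". For primary and specialised care, "Records of patient activity will be obtained from Osakidetza’s information systems".

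**The concern.** Time passes between assignment and the last 30 days of life, and a carer can die or become disabled in that time. The article itself links this event to both sides of the comparison. Its Background says that home visits depend on a sound care structure around the patient and that the supply of informal carers is shrinking. It also lists carer respite and prevention of burnout among the needs that belong to social support. Losing the carer is therefore a plausible route to hospital use, and one that SAIATU might make less common.

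If such patients were excluded after assignment, the analysis would condition on something that may lie on the path from programme to outcome. Part of a real effect could be removed, harm could be hidden, or a difference could appear where there is none. The balance that randomisation provides would no longer be guaranteed.

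**Working it through.** **1. Does each criterion do anything at baseline?**

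- *Carer death.* A patient whose only carer has died already fails the carer-presence criterion. The separate exclusion adds something mainly if the death comes after entry.
- *Carer disability.* This can exist at screening or arise later.
- *Withdrawal from the public system.* Patients must already be under the Basque Health Service, so the criterion adds little at entry. The word itself suggests a later event.

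**2. Would the event stop the outcome from being observed?**

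- *Carer death or disability: no.* Primary and specialised care use comes from Osakidetza's systems, and Home Hospitalisation staff record their own activity. Neither source depends on the carer.
- *Withdrawal from the public system: yes, at least in part.* Use outside the system is not recorded. This is a missing-data problem of a different kind.

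**3. Size.** The article has no figure on this point. Its approximate total of 150 is provisional (150/1,478 = 10.1% of the deaths it expects in 10 months), and it gives no split between cohorts. All rates and day counts below are assumptions, as is 75 per cohort.

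*(a) SAIATU works only by preventing carer loss.* Let D be the extra hospital days per carer loss, and eS and eC the proportions losing a carer in the SAIATU and control cohorts. The difference among all assigned patients is (eS − eC) × D. After exclusion it is 0 by construction.

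| D (days) | eC 10%, eS 5% | eC 15%, eS 5% | After exclusion |
|---|---|---|---|
| 3 | −0.15 | −0.3 | 0 |
| 5 | −0.25 | −0.5 | 0 |
| 8 | −0.4 | −0.8 | 0 |
| 12 (20 v 8 days) | −0.6 | −1.2 | 0 |

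Check of the last row at 10% v 5%: control 0.90 × 8 + 0.10 × 20 = 9.2; SAIATU 0.95 × 8 + 0.05 × 20 = 8.6; difference −0.6. If the split is reversed, the same exclusion hides harm of the same size. If eS = eC, nothing is lost.

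*(b) No true effect, but exclusion is linked to severity.* Simulation: the outcome is a standard normal severity score, and the chance of exclusion rises with severity (slope 0.5 or 1.0 on the probit scale). Bias is the SAIATU minus control mean among those left. Its standard error is √(1/[75(1 − eC)] + 1/[75(1 − eS)]).

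| eC v eS | Bias (SD), slope 0.5 | Type I error | Bias (SD), slope 1.0 | Type I error |
|---|---|---|---|---|
| 10% v 10% | 0.00 | 5% | 0.00 | 5% |
| 15% v 5% | 0.075 | 7.2% | 0.117 | 10.4% |
| 20% v 10% | 0.069 | 6.7% | 0.110 | 9.5% |

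The sign is against SAIATU here because the control cohort loses more of its severe patients. It reverses if the rates do.

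*(c) Loss of numbers alone.* With 75 per cohort, the difference detectable with 80% power is (1.960 + 0.842) × √(2/75) = 0.457 SD. Removing 5%, 10%, 15% or 20% of each cohort lowers power for that difference to about 78%, 76%, 73% or 71%.

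**The case against.** The strongest reply is that this is an eligibility list and should be read as one. Its heading speaks of the study sample, and its consent item is ordinarily an entry condition. Neither the Phase 2 description nor Analysis of variables says that an assigned patient leaves the cohort or the analysis. A full protocol or SAP may settle how later events are handled, and its absence here is no fault of the article.

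A reader might infer that the two criteria can only act after enrolment, and that randomised patients will therefore be dropped. The documents do not support that. Disability of the carer can predate screening, and a patient may have left the public system before entry. The inclusion item speaks of a principal carer and the exclusion item of a family carer. Since the Background recognises professional as well as family carers, even a carer's death could have a baseline meaning.

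It is also fair that illustration (a) returns zero by design, that none of the assumed rates comes from the article, and that hospital use is only part of the main variable: four of the eight primary and specialised care measures are home or clinic visits.

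These replies limit how firmly the point can be put, but they do not remove it. The objection is to criteria that the article states, not to an analysis set that it leaves out. Next to the entry conditions, their most natural use is after assignment, and someone following the text could remove patients on that basis.

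**Conclusion.** The point holds as a conditional risk. Two of the three exclusions have no time of application and read most naturally as events after assignment. Applied that way, they remove randomised patients for reasons plausibly related to hospital use and to the intervention, which may bias the comparison.

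The documents do not establish that bias will occur. Its size and direction cannot be derived from them, and bias from differential exclusion is nil when rates and mechanism are the same in both cohorts. The figures of 0.07 to 0.12 SD and a type I error of 7% to 10% rest on an assumed 10-point difference in exclusion, a link to severity, and 75 patients per cohort.

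The two criteria also need different handling. Carer loss gives no data reason to exclude anyone, whereas withdrawal from the public system mainly costs outcome data. The wording should be changed, because the correction is cheap and protects the main comparison.

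**What to change.** 1. State that both criteria are assessed only before assignment.
2. State that a patient whose carer later dies or becomes disabled stays in the assigned cohort and is analysed with the Osakidetza records for the last 30 days of life.
3. Treat later withdrawal from the public system as missing outcome data. Report the number by cohort, do not count unobserved use as zero, and run a sensitivity analysis that varies the unobserved use over a plausible range, separately in each cohort. Simply analysing whatever was recorded up to the last entry would not do, because it treats use outside the system as none.

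The cost is a few sentences in the protocol and one sensitivity analysis. No extra visits are needed, since the records are already planned. The downside is that a few patients will have incomplete records. Reporting carer loss by cohort would be informative, but the article plans only to characterise the principal carer, so it would need added follow-up of carers and is not part of this change.
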